### Sample size

This study aims to assess the usefulness of RI. The number of patients should be considered as a continuous variable, which contributes to the precision of the estimates of the results: –Means, course secondary to treatments, based on anterior studies using the delta (Day 1 – week 7) on the PCL-S score. One should expect a pre−/post-treatment PCL-S difference of 30 points with a SD of 15–25 points [7]. If a symptom reduction of 5–9 points on the PCL-S represents a favorable response and a reduction greater than 10 represents a clinically meaningful reduction, one should expect that 70% of patients display a favorable response to the RT treatment [7]. Based on those results, the confidence intervals will evolve according to the plot proposed below. For example, a 95%CI calculated over 200 patients will vary between 27 and 33.

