## Methods

### Study design

This study is a two-arm non-randomized, multicenter controlled trial, comparing RT to TAU for the treatment of trauma-related disorders. As shown in Table 1, psychometric assessments are made at baseline, after 6 weeks of treatment, as well as 3 and 12 months following study inclusion. In order to enhance external validity this study protocol is implemented into the usual healthcare system in France. Patients are offered the choice of the intervention they wish to receive. The study protocol was approved by local ethics committee (*Comité de protection des personnes* for Ile de France VI #CPP/14–16), and regulatory agencies (*Commission nationale de l’informatique et des libertés* #GPR1713292F and *Agence nationale de sécurité du medicament.* We plan to include up to 400 participants with the possibility of stopping at the end of the pre-specified inclusion period if at least 200 receiving RT are enrolled.

**Table 1 Tab1:** Overview of measures and time of assessment

Instrument	Variable	T0	Treatment sessions						T1	T2	T3
			t1	t2	t3	t4	t5	t6			
Demographics	*Sociodemographic characteristics*	X									
PCL-S	*PTSD symptom severity*	X	x	x	x	x	x	x	X	X	X
CGI	*Global patients’ condition*	*	x	x	x	x	x	x	*	*	*
MINI-S	*Diagnosis and comorbidities*	X							X	X	X
PDI	*Severity of trauma exposure*	X									
PDEQ	*Peritraumatic dissociation*	X									
WHOQOL-BREF	*Quality of life*	X							X	X	X
EQ-5D-5 L	*Quality of life*	X							X	X	X
MEDEC	*Health service utilization*	X							X	X	X
HSCL-25	*Anxiety and depressive symptoms*	X							X	X	X
QFS	*Social functioning*	X							X	X	X

*Assessed by a clinician blind to the patient’s treatment modality

T0: baseline assessment

T1: posttreatment assessment (week 7)

T2: 3-month follow-up assessment

T3: one-year follow-up assessment

PCL-S: PTSD Checklist – Specific Version, CGI: Clinical Global Impression, MINI-S: Mini International Neuropsychiatric Interview for DSM-5, PDI: Peritraumatic Distress Inventory, PDEQ: Peritraumatic Dissociative Experiences Questionnaire, WHOQOL-BREF: World Health Organization Quality of Life (brief), EQ-5D-5 L: EuroQol Questionnaire, MEDEC: Medico-Economic Questionnaire, HSCL-25: Hopkins Symptom Checklist, QFS: Social Functioning Questionnaire

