### Instruments

The primary outcome for the effectiveness analysis is the difference between the group mean PTSD Checklist-Specific (PCL-S) score at inclusion (T0) minus the same score obtained at the one-year follow-up (T3). The PCL-S will be administered at baseline (T0), at each treatment session (t1-t6) and 1 week posttreatment (T1), 3-month follow-up after baseline (T2) and one-year follow-up after baseline (T3).

The reliable and valid PCL-S [32, 33] is a 17-item self-report scale that assesses DSM-IV-TR PTSD symptoms in the past week from the perspective of the patient. (No validated French PCL version compatible with the DSM-5 was available when the study began). The PCL-S ranges between 17 (no symptom) and 85 (maximum score). For study inclusion, a cut-off score of equal or greater than 44 is used, as done by others [34, 35] (Fig. 2).

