### Statistical analyses

The clinical scores will be analyzed using an intention to treat (ITT) analysis: all patients allocated to RT or TAU will be analyzed. The collected data will be used to describe the 2 cohorts: the RT group and the TAU group. Variables will comprise socio-demographic parameters, duration of PTSD, psychiatric comorbidities, pre-morbid disorders, and co-prescriptions. As described above, the primary outcome for effectiveness analysis is based on the delta (T3 minus T0) of PTSD *symptom severity* (PCL-S). A first indicator will be the mean PCL- S difference between T3 and T0. The delta of EQ5D-5 L (T3 minus T0) examines efficiency from the health economic perspective.

A regression model will be used to calculate a second indicator based on the PCL-S values (t1-t6) collected between T0 and T1, allowing for the evaluation of PTSD symptoms evolution over time and its variation between individuals. A third indicator will be the rate of patients considered as treatment responders (PCL-S score < 44) at Week 7 (T1), Week 13 (T2) and Week 52 (T3). Mean and SD will also be computed for the delta of CGI score between T1 and T0. Missing data will be replaced using multiple imputation methods, provided that the data is missing at random or completely at random.

Additionally, in order to take into account the difference between the features of both cohorts (RT and TAU), we will use a propensity score of being allocated to RT to adjust the different model. For the secondary criteria, these propensity scores will be applied to the other scales used for the assessment.

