The absence of randomization could be considered a limitation. However, this choice is in line with the choice of a pragmatic trial, and ensures feasibility, considering that –based on our prior experience- we expect that patients will express a preference for RT compared to TAU. Due to the extraordinary circumstances in which this study was initiated, we felt that it would be wiser to conduct the trial by asking the study participants to express their preference toward the treatment they wished to receive (RT or TAU). Ultimately, the choice of treatment of the participants will inform us as to the treatment acceptability of RI. Additionally, recruitment would be easier using a free choice approach. As mentioned previously, a regression model highlighting the course of PTSD symptom severity over time will allow us to measure the proportion of patients responding to treatment and achieving remission. The comparison of the two treated cohorts will involve a propensity score of choosing RT treatment, in order to take into account measurable confusion factors and compensate for the absence of randomization. Also, to limit selection bias, eligibility criteria are the same for the two groups, except for contra-indications to propranolol. In the context of the terrorist attacks and ensuing mass suffering, and given the existence of efficacious treatments (SSRIs or psychotherapies), this effectiveness study is not compatible with the implementation of a placebo arm. A placebo controlled trial was recently published and showed the efficacy of RT versus placebo [7].

The absence of blinding is another limitation in our study. Neither the patients nor the assessors are blind for the primary criterion of assessment (PCL-S score), as is always the case in psychotherapy research. A single-blind pre/post evaluation is conducted for the CGI criterion, with the same rater who does not participate in the patient’s care. In addition, because the main outcome is a PTSD symptom self-report –and not a clinician-based interview- there is no interviewer bias.

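### The sample-size section gives single-group week-7 precision, but the main question is a one-year RT versus TAU comparison, and the enrolment-closing rule sets a minimum for RT only

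*Protocol article*

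**What the plan says.** All references are to the protocol article.

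- **Basis of the sample size (Sample size).** The number of patients is treated as a matter of precision, "based on anterior studies using the delta (Day 1 – week 7) on the PCL-S score". The expected result is a "PCL-S difference of 30 points with a SD of 15–25 points", and the response statement concerns one treatment: "one should expect that 70% of patients display a favorable response to the RT treatment". The worked example is "For example, a 95%CI calculated over 200 patients will vary between 27 and 33".
- **Primary outcome (Instruments; Statistical analyses).** The baseline PCL-S score is taken "minus the same score obtained at the one-year follow-up (T3"). The analysis section repeats that "the primary outcome for effectiveness analysis is based on the delta (T3 minus T0) of PTSD" symptom severity.
- **Comparative purpose.** The Background lists effectiveness and cost-utility of RT against TAU among the aims. Study design describes a two-arm controlled trial. Statistical analyses plans propensity-score adjustment and between-group tests of QALYs and costs. The Discussion speaks of non-inferiority to TAU.
- **Enrolment (Study design).** Up to 400 patients, with the "possibility of stopping at the end of the pre-specified inclusion period if at least 200 receiving RT are enrolled". No corresponding number is given for TAU.
- **Allocation (Procedure; Discussion).** The arm follows the patient's choice and eligibility for RT, and "we expect that patients will express a preference for RT compared to TAU".

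**The concern.** The only precision figure in the plan differs from the main question in two ways. It stops at week 7 where the primary outcome runs to one year, and it describes one group where the aims need a difference between two.

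The closing rule has the same one-sided focus. It secures the RT arm, which the plan expects to fill easily, and leaves the TAU arm, which the plan expects to be less popular, without a floor. The precision of a difference is governed mainly by the smaller arm. The trial could therefore close fully on plan, quote about ±3 points, and hold a TAU arm too small to support the effectiveness, non-inferiority or cost-utility conclusion.

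**Working it through.** **Inputs.** From Sample size: mean change 30, SD 15 to 25, n = 200, 95% interval. From Study design: cap of 400, at least 200 on RT, no TAU minimum. Assumed here, because the article does not give them: the TAU counts, a one-year SD equal to the week-7 range, and a 30% loss at one year used for scale.

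**Step 1: reproduce the plan's figure.** Single mean: 30 ± 1.96 × SD / √200.

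| SD | Half-width | Interval |
|---|---|---|
| 15 | 2.08 | 27.9 to 32.1 |
| 20 | 2.77 | 27.2 to 32.8 |
| 25 | 3.46 | 26.5 to 33.5 |

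A half-width of exactly 3 corresponds to SD = 3 × √200 / 1.96 = 21.6. A half-width that rounds to 3 (2.5 to 3.5) corresponds to SDs of about 18.0 to 25.2. The plan's 27 to 33 is thus a sound whole-point summary of a one-sample interval. It cannot be an interval for the RT-TAU difference, which would be centred on that difference and not on 30.

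**Step 2: the comparison.** Half-width of the difference in mean change: 1.96 × SD × √(1/n_RT + 1/n_TAU). For 200 v 50 at SD 20, this is 39.2 × √(0.005 + 0.02) = 39.2 × 0.158 = 6.2.

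| RT v TAU | SD 15 | SD 20 | SD 25 |
|---|---|---|---|
| 200 v 200 | 2.9 | 3.9 | 4.9 |
| 320 v 80 | 3.7 | 4.9 | 6.1 |
| 200 v 50 | 4.6 | 6.2 | 7.7 |
| 200 v 20 | 6.9 | 9.2 | 11.5 |

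Every row is permitted by the plan. The 320 v 80 row shows that reaching the cap of 400 does not restore the precision of an even split.

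**Step 3: losses.** If 30% of one-year scores were missing in both arms, each entry would be multiplied by 1/√0.7 = 1.20. For 200 v 200 at SD 20, the half-width goes from 3.9 to 4.7. Any efficiency lost through propensity-score adjustment comes on top and is not quantified here.

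**Step 4: why no TAU minimum is proposed as a number.** Suppose, purely for illustration, a target half-width of 5 points with 200 RT patients enrolled.

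- Full retention: 1/n_TAU = (5 / (1.96 × SD))² − 1/200, which gives 89 TAU patients at SD 20 and 185 at SD 25.
- 30% loss: 140 RT patients remain. The requirement is 110 TAU completers at SD 20 (110 / 0.7, about 157 enrolled) and 306 at SD 25 (306 / 0.7, about 437 enrolled). The last figure exceeds the cap.

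The minimum therefore depends heavily on the target, the SD and retention, all of which are for the sponsor to set.

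**The case against.** The best defence is that the section openly sizes the trial by precision, claims no comparative power, and that the primary outcome is worded as a change from baseline to one year, with the propensity-score comparison introduced as an addition. Precision-based sizing is legitimate, and it is true that the outcome definition does not itself name an RT-TAU difference. The comparison comes from the aims, the controlled design, the between-group tests and the non-inferiority statement. That removes any charge that the section promises something false. It does not remove the mismatch: the time point is still week 7 and not one year, and the comparative aims cannot be met from the RT arm alone. Nor is this a detail left to an analysis plan, because the article itself states both the justification and the closing condition, and a later document cannot recover TAU patients who were never enrolled.

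Four stronger readings are tempting and are not supported:

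- **That 27 to 33 is an arithmetic error, or fails at SD 25.** It does not: 26.5 to 33.5 is the same interval at whole-point rounding. Only the low end of the SD range (27.9 to 32.1 at SD 15) visibly departs from it. As a week-7 figure it also makes no assumption about missing one-year data.
- **That the half-widths should be judged against the 5–9 and over-10-point thresholds.** In Sample size these describe reductions in individual patients. They are not between-group differences or margins.
- **That the closing rule is an interim stop.** It is optional and applies only at the end of the pre-specified inclusion period.
- **That the TAU arm will be small.** The plan expects a preference for RT but does not forecast the split. The point is that nothing guards against a small TAU arm.

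**Conclusion.** The concern holds as a mismatch between the stated precision and the quantity the trial is meant to estimate, together with a closing condition that covers one arm only. The quoted interval is correct for what it measures, but it measures a single group at week 7. For the one-year RT-TAU difference, the plan allows 95% half-widths from 2.9 points (200 v 200, SD 15) to 11.5 points (200 v 20, SD 25). At SD 20 with 200 RT patients, the figure is 3.9 with 200 TAU patients and 6.2 with 50.

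These sizes assume that the week-7 SD range carries over to one year, that nobody is lost, and that propensity-score adjustment costs nothing. The TAU counts are illustrative. The conclusion itself needs none of these assumptions: it follows from the time point, the single-group formula and the absence of a TAU minimum.

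**What to change.** **Sample size.** Label 27 to 33 as single-arm precision at week 7, and give its range over the stated SDs (27.9 to 32.1 at SD 15; 26.5 to 33.5 at SD 25). Add the expected half-width of the RT-TAU difference in one-year PCL-S change, over the plausible splits between arms and plausible retention.

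**Study design.** Make the closing condition depend on both arms within the cap of 400, with a TAU minimum derived from the sponsor's own target precision and expected retention. State that, if the minimum is not reached, the RT-TAU results will be reported as descriptive, without a comparative or non-inferiority claim.

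**Cost.** Changes of wording, and no enrolment beyond the planned 400. The stated precision will look less favourable. If the sponsor's target proves unattainable within the cap, that has to be said and the comparative claim limited accordingly.

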## Discussion

The fight against terrorism should involve all mental health specialties. To fulfill that role, effective and innovating multimodal treatments are required. At its conclusion, Paris MEM will become the largest pragmatic trial to date assessing whether RT works under the usual healthcare practice that prevails in the aftermath of a large-scale man-made disaster (effectiveness). Paris MEM aims to determine if RT can become the preferred first-line therapeutic intervention for traumatic stress following a wide scale catastrophic event, considering that it is easy to teach to clinical staff and may treat trauma-related disorders using a lesser amount of time and resources than TAU (efficiency). RT could reinforce the therapeutic arsenal for the treatment of PTSD patients, not only for communities in western countries but also worldwide for terror- or disaster-stricken communities who wish to undo some of the psychological damage they sustained.

One of the aims of the Paris MEM study is to provide an educational phase on an innovative therapeutic method able to help practitioners of the various healthcare institutions of Paris to treat PTSD. While building the experimental design, one of our main concerns was the feasibility and acceptability of the treatment procedure from the therapists’ and patients’ perspectives. As mentioned in the Methods section, one of the main outcomes will combine cost and effectiveness 1 year following the treatment. In that sense, we aim for a non-inferiority procedure compared to TAU, hoping for a better cost-utility outcome of the RT method.

The absence of randomization could be considered a limitation. However, this choice is in line with the choice of a pragmatic trial, and ensures feasibility, considering that –based on our prior experience- we expect that patients will express a preference for RT compared to TAU. Due to the extraordinary circumstances in which this study was initiated, we felt that it would be wiser to conduct the trial by asking the study participants to express their preference toward the treatment they wished to receive (RT or TAU). Ultimately, the choice of treatment of the participants will inform us as to the treatment acceptability of RI. Additionally, recruitment would be easier using a free choice approach. As mentioned previously, a regression model highlighting the course of PTSD symptom severity over time will allow us to measure the proportion of patients responding to treatment and achieving remission. The comparison of the two treated cohorts will involve a propensity score of choosing RT treatment, in order to take into account measurable confusion factors and compensate for the absence of randomization. Also, to limit selection bias, eligibility criteria are the same for the two groups, except for contra-indications to propranolol. In the context of the terrorist attacks and ensuing mass suffering, and given the existence of efficacious treatments (SSRIs or psychotherapies), this effectiveness study is not compatible with the implementation of a placebo arm. A placebo controlled trial was recently published and showed the efficacy of RT versus placebo [7].

The absence of blinding is another limitation in our study. Neither the patients nor the assessors are blind for the primary criterion of assessment (PCL-S score), as is always the case in psychotherapy research. A single-blind pre/post evaluation is conducted for the CGI criterion, with the same rater who does not participate in the patient’s care. In addition, because the main outcome is a PTSD symptom self-report –and not a clinician-based interview- there is no interviewer bias.

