Costs will be estimated from the point of view of society for the follow up period (1 year) without discounting, due to the study duration. We will estimate in each group the median cost, mean and 95% confidence interval (95%CI) using bootstrap replications because of distribution skewedness and calculate the cost difference. Health-related QOL is collected using the EQ-5D-5 L self-administered questionnaire at baseline, at 3 months and at 1 year. The utility values will be based on French tariffs. The efficacy of the intervention will be estimated by quality adjusted life years (QALYs), using the EQ-5D-5 L scores and the time between treatment sessions. The difference in QALYs is the difference in the area between the utility curves for the two groups. Between-group comparisons of QALYs and costs will be performed with the appropriate statistical tests for their distribution, with a significance threshold of .05 (two-sided test).

The incremental cost utility ratio is the difference in average total costs divided by the difference in average total QALYs. The joint comparison of costs and effects will use nonparametric bootstrapping with 1000 resamples and generate the scatterplot on the cost effectiveness plane as a well as an acceptability curve.

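### The Discussion announces a non-inferiority procedure against TAU, but the Methods give no endpoint, margin or decision rule for one, so a null difference could not support the claim

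*Protocol article*

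**What the plan says.** The non-inferiority aim appears once, in the Discussion. After noting that "one of the main outcomes will combine cost and effectiveness 1 year following the treatment", the article continues: "we aim for a non-inferiority procedure compared to TAU, hoping for a better cost-utility outcome of the RT method".

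The sections that would have to carry this aim say the following.

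- **Efficacy, effectiveness and efficiency; Study design.** The co-primary aims are effectiveness and efficiency. No non-inferiority hypothesis is named. Up to 400 patients are planned. Enrolment may stop at the end of the inclusion period once at least 200 have been enrolled on RT. No minimum is set for TAU.
- **Statistical analyses, clinical scores.** "The clinical scores will be analyzed using an intention to treat (ITT) analysis: all patients allocated to RT or TAU will be analyzed". The effectiveness outcome is "based on the delta (T3 minus T0) of PTSD" symptom severity on the PCL-S, with propensity-score adjustment. No margin or rule for a between-group conclusion is given. The Instruments section defines the same change the other way round, as T0 minus T3.
- **Statistical analyses, economic part.** "Between-group comparisons of QALYs and costs will be performed with the appropriate statistical tests for their distribution, with a significance threshold of .05 (two-sided test"; costs and effects are then compared jointly by bootstrap, with a cost-effectiveness plane and an acceptability curve.
- **Sample size.** The number of patients is justified by the precision of a pre/post PCL-S change from day 1 to week 7: 30 points with an SD of 15 to 25, and a 95% CI of 27 to 33 with 200 patients.

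**The concern.** A non-inferiority conclusion needs a named endpoint, a margin fixed in advance and a rule that compares a confidence bound with that margin. The article announces the conclusion, but its analysis and sample-size sections follow a different framework of estimation and difference testing. This goes beyond detail that an analysis plan could fill in, because the sample-size section gives its rationale explicitly and that rationale contains no comparison with TAU.

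Without a margin, the result most readily offered in support would be a non-significant difference. Such a result becomes easier to obtain as the TAU arm shrinks. The design leaves the TAU arm unprotected: patients choose their treatment, the Discussion expects them to prefer RT, and only RT has a recruitment floor. The Discussion also says the trial aims to determine whether RT can become the preferred first-line intervention, so the error would touch the main message.

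**Working it through.** **1. The plan's own figure.** A one-sample interval is 30 ± 1.96 × SD / √200.

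| SD | Half-width | 95% CI |
|---|---|---|
| 15 | 2.08 | 27.9 to 32.1 |
| 20 | 2.77 | 27.2 to 32.8 |
| 25 | 3.46 | 26.5 to 33.5 |

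A half-width of exactly 3 needs SD = 3 × √200 / 1.96 = 21.65. The stated 27 to 33 therefore reproduces at an SD of about 20 to 22, inside the stated range. The sizing is single-group precision; TAU does not enter it.

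**2. What a non-significant difference would mean.** Inputs and assumptions:

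- The SD of the change is 15, 20 or 25 (Sample size section), assumed equal in both arms and carried from week 7 to one year.
- The true RT disadvantage is 5 PCL-S points. This is an assumption; 5 is the lower end of the range that the Sample size section calls a favorable response in a patient, not a between-group margin.
- The arms are 200 + 200 (an equal split of 400) or 200 + 50 (an assumed split; the documents fix none).

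SE = SD × √(1/n_RT + 1/n_TAU), which is SD × 0.1000 for 200 + 200 and SD × 0.1581 for 200 + 50.

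P(non-significant) ≈ 1 − Φ(5/SE − 1.96).

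| Arms | SD 15 | SD 20 | SD 25 |
|---|---|---|---|
| 200 + 200: SE | 1.50 | 2.00 | 2.50 |
| 200 + 200: P(non-significant) | 8.5% | 29.5% | 48.4% |
| 200 + 50: SE | 2.37 | 3.16 | 3.95 |
| 200 + 50: P(non-significant) | 44.1% | 64.8% | 75.6% |

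**3. Whether the size would suffice.** With truly equal arms and a one-sided 2.5% level, power = Φ(margin/SE − 1.96). The margins are assumptions taken from the 5- and 10-point thresholds in the Sample size section.

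| Margin | Arms | SD 15 | SD 20 | SD 25 |
|---|---|---|---|---|
| 5 | 200 + 200 | 91.5% | 70.5% | 51.6% |
| 5 | 200 + 50 | 55.9% | 35.2% | 24.4% |
| 10 | 200 + 200 | over 99% | 99.9% | 97.9% |
| 10 | 200 + 50 | 98.8% | 88.5% | 71.6% |

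For 80% power, n per arm = 2 × SD² × (1.96 + 0.84)² / margin². This gives 142 / 252 / 393 at margin 5 and 36 / 63 / 99 at margin 10. Adequacy turns on the missing margin and the unfixed TAU number. Steps 2 and 3 ignore dropout and the variance cost of propensity adjustment.

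**4. The sign of the change.** With T3 minus T0, improvement is negative and the adverse bound of RT minus TAU is the upper one. With T0 minus T3 it is the lower one. The article uses both definitions, so a bound rule could not be written without choosing one.

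**The case against.** The strongest reply is that one loose sentence in a Discussion is not the governing hypothesis. The aims, design, analysis and sample-size sections never use the term, and they describe a coherent estimation and cost-utility study. The sentence refers to the combined cost and effectiveness outcome, and the planned bootstrap handles joint uncertainty in costs and QALYs without needing a margin. That much is fair. It supports deleting the sentence, but it does not make the sentence consistent with the Methods.

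Other parts of the reply also stand, and they limit what may be inferred.

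- A reader might infer that the plan tests PCL-S with a two-sided .05 difference test. The documents state that test for QALYs and costs only. Nor is it incompatible with non-inferiority in itself, since a two-sided 95% CI would serve once a margin existed.
- A reader might infer that naming only ITT biases the trial towards non-inferiority, through switching between arms or imputation under missing at random. The article describes no switching. The effect of imputation depends on a model it does not give. A per-protocol analysis may sit in a document not shown, and in a patient-choice study selection on adherence brings its own confounding.
- A reader might infer that the sponsor intends to read a null result as non-inferiority. No passage says so; the point is that nothing in the plan rules it out.
- The sign mismatch is secondary. Lower PCL-S is better, so the harmful direction is clear under either definition.

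**Conclusion.** The point holds as a conflict within the article: a stated non-inferiority aim against Methods that provide no endpoint, margin, decision rule or matching sample-size rationale. A non-significant RT-TAU difference would not support the claim. With an assumed true disadvantage of 5 PCL-S points and an SD of 15 to 25, such a result would arise about 8.5% to 48% of the time at 200 + 200, and 44% to 76% at an assumed 200 + 50.

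These figures use PCL-S because it is the only outcome for which the article gives an SD. The Discussion sentence does not make clear whether PCL-S, EQ-5D or QALYs would be the non-inferiority endpoint. The 5-point difference and the 200 + 50 split are illustrations, not values from the plan.

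The tempting stronger conclusion, that 400 patients are too few for non-inferiority, is not supported. Under a 10-point margin and an equal split, power would be about 98% even at SD 25. Under a 5-point margin it could be as low as 52% with the same split.

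**What to change.** Choose one of two courses before analysis.

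1. **Drop the claim.** Delete the non-inferiority sentence. Report the propensity-adjusted RT-TAU difference with its 95% CI, and state that a non-significant difference will not be read as non-inferiority.
2. **Specify the claim.** Name the non-inferiority endpoint. Use one sign convention for the change score in both Instruments and Statistical analyses. Set a margin that the sponsor justifies, and require the adverse-side 95% bound of the propensity-adjusted difference to exclude it. State the power that results for the actual arm sizes. A per-protocol analysis may be added as support but is not essential.

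The cost is one sentence under the first course and about one paragraph under the second. The downside is that the non-inferiority claim is either given up or becomes harder to reach, particularly if the TAU arm turns out small.
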